### Statistical methods

Study assessments will be completed prior to randomisation (T0), prior to the initiation of the intervention (T1), and after completion of the intervention period at the 12-month follow-up (T2).

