### Programme implementation

The project will be led and supported by multidisciplinary teams at each institution, including paediatric neurologists/rehabilitation specialists, paediatric ophthalmologists/optometrists, paediatric developmental therapists, paediatric physiotherapists and occupational therapists.

The initial eligibility confirmation and baseline assessments will take place at the respective recruiting centre. Medical needs and treatable eye problems (refractive correction, other preventative measures) will be addressed prior to the onset of the study period by a Paediatric Ophthalmologist/Optometrist for infants in both groups. On confirmation of eligibility and completion of baseline assessments, the family will be randomly allocated to SCC or VISIBLE.

For the intervention group, appointments every 2 weeks will be provided by VISIBLE-trained developmental therapists to contextualise the programme to the infant’s natural environment and support parents with implementation. The first home visit for the VISIBLE group families will include parent training and information about and demonstration of activities appropriate for their infant. The following visits (90–120 min duration) will include direct activities with the parents and infant, coaching the advancement of activities to accommodate the infant’s emerging skills and parent treatment fidelity checks. The information discussed during the visits will be also available to the parents in the form of a study-specific parent booklet. It consists of modules that will be provided to the parent based on the needs of the infant and the family.

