### Blinding

Trained outcome assessors and data analysts will be masked to the group allocation of the individual participants. Due to the nature of the intervention, the parents and therapists providing intervention visits cannot be masked to group allocation. Baseline data will be collected prior to randomisation (T0).

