#### Secondary outcome measures

The Peabody Developmental Motor Scales, Second Edition (PDMS-2)^38^ at T1, T2 is a standardised and normed scale for children aged from birth to 6 years and has been validated for use as a discriminative measure. Infant primary motor outcomes at 12 months CA will be assessed using the PDMS-2, a standardised, norm-referenced measure used to evaluate the gross and fine motor development of children aged birth to 6 years.

The Bayley Scales of Infant and Toddler Development, Third Edition (BSID-III)^39^ at T2, a standardised and norm-referenced assessment of cognitive, motor, language and social-emotional development of infants and toddlers 0–3 will be assessed using the gold standard Bayley Scales of Infant and Toddler Development, Third Edition. These assessments will be supplemented by parent report on the norm-referenced forms.

The COPM^40^ at T1, T2 is used to assist parents in setting and prioritising goals and measuring parent-perceived change of their infant’s performance of the goal and own satisfaction with progress. The semi-structured initial interview to establish the goals will focus on what aspects of the infant’s vision behaviour the parent wants or needs to see improved.

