Pediatric Evaluation of Disability Inventory-Computer Assisted Test (PEDI-CAT)^41^ at T1, T2 is a parent-reported measure of their child’s independence in self-care, mobility and social function that has been analysed in both children with disabilities and those with typical development. Raw scores will be converted to standardised scores using normative data (0–100) to measure change in function. Developmental outcomes in self-care, mobility and social function will be assessed at 12 months CA using the PEDI-CAT, a standardised, norm-referenced assessment of independence in self-care. The instrument measures functional outcomes across four domains: daily activities, the ability to perform living skills; mobility, the ability to move around the home and in the community; and social/cognitive, the ability to participate and effectively engage in social situations. Responsibility, the fourth domain, will not be assessed in this study.^42^ The PEDI-CAT has good discriminant validity in CP populations, between children with and without disability, and demonstrates concurrent validity with the Wee-FIM (Functional Independence Measure for Children) in children with brain injury and developmental disabilities.^43^ The test is valid, reliable and responsive in this population, takes 10–15 min to complete and requires no formal training.

DASS-21^30^ at T1, T2 is a 21-item questionnaire that assesses symptoms of depression, anxiety and stress in the parent/caregiver.

Emotional Availability Scales (EAS) and Self Report^31^ at T1, T2 is based on a naturalistic observation of a parent-infant interaction in the family’s home to measure parental sensitivity, parental structuring, parental non-intrusiveness, parental non-hostility, child responsiveness and child involvement, and a global relationship quality rating. The video will be 15 min long. Parents will be asked to video the interaction, or telemedicine video recording will be used. The EAS will be assessed by an independent rater trained in scoring the EAS. The EAS self-report is a 32-item parent-report measure of emotional availability within the parent-child relationship.

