### Data analysis plan

A multisite RedCap programme database will be used for this study. Study personnel at each site will enter the data onto RedCap, a secure web platform for the construction and management of surveys and online databases. All the data of the same patient will be collected under an ID number. Videos of sessions will be taken to ensure fidelity of intervention visits provided by the study therapists.

All measures will be undertaken to avoid missing data for the primary outcome. Rescheduling of appointments for assessments will be done if the data collection cannot be completed in one appointment. Should vital data be missing, use of all available data will be used, as recommended through methods such as multiple imputation and likelihood-based analysis.

Statistical analysis will be conducted using SPSS following standard methods for RCTs. Intention-to-treat analysis will be applied to minimise inflation of treatment effects, consistent with Consolidated Standards of Reporting Trials (CONSORT) guidelines.^46^ Descriptive statistics will be used to summarise baseline characteristics and outcome measures for both treatment groups, with continuous variables reported as means and SDs (if normally distributed) or medians and IQRs (if skewed), and categorical variables as frequencies and percentages. Normality of continuous data will be assessed using the Shapiro-Wilk test and visual inspection of histograms and quantile-quantile (Q-Q) plots. If data are normally distributed, intervention efficacy will be tested using general linear models, specifically Analysis of Covariance (ANCOVA), adjusting for baseline values. If substantial skewness is observed and not resolved through transformation, non-parametric alternatives such as the Mann-Whitney U test for between-group comparisons will be used. Appropriate adjustments for multiple comparisons will be applied where necessary.

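### The article contradicts itself on when six secondary measures get their baseline: T1 is their only pre-treatment value, and nothing places T1 before randomisation

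*Protocol article*

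**What the plan says.** **Time points.** Statistical methods lists three. The first two are given as "Study assessments will be completed prior to randomisation (T0), prior to the initiation of the intervention (T1"; the third, T2, follows the intervention period. Only T0 is tied to randomisation.

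**Schedule by instrument.** Under Primary outcome measure, vision is assessed at T0 and T2. Under Secondary outcome measures, MRI is at T0 and T2 and the Bayley scales at T2 only. Six other instruments carry the label T1, T2. Two examples are PDMS-2 ("at T1, T2 is a standardised and normed scale for children aged from birth to 6 years") and DASS-21 ("at T1, T2 is a 21-item questionnaire that assesses symptoms of depression, anxiety and stress in the parent/caregiver"). COPM, PEDI-CAT, EAS with its self-report, and ITQOL are labelled in the same way.

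**Order of baseline and allocation.** Blinding says: "Baseline data will be collected prior to randomisation (T0". Programme implementation says: "On confirmation of eligibility and completion of baseline assessments, the family will be randomly allocated to SCC or VISIBLE".

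**Masking and analysis.** Blinding states that "the parents and therapists providing intervention visits cannot be masked to group allocation". The Data analysis plan specifies "Analysis of Covariance (ANCOVA), adjusting for baseline values" and does not say whether baseline means T0 or T1.

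**The concern.** A baseline covariate is safe in a randomised comparison because allocation cannot have influenced it. For the six instruments at T1 and T2, the article does not secure this.

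If T1 falls after allocation, three things are at stake:

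- **Reporting.** COPM, PEDI-CAT, DASS-21, the EAS self-report and ITQOL come from parents. Hope or disappointment on learning the arm could shift their answers.
- **Goal setting.** COPM goals are set at the initial interview. If parents choose them knowing the arm, the goals themselves may differ between arms, and no covariate repairs that. COPM also feeds the acceptability evaluation.
- **Missing baselines.** A family that withdraws between allocation and T1 has no baseline on any of the six, in a trial of 32 that allows for up to 25% withdrawal.

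In addition, T1 is defined by the start of an intervention that standard-care infants never start, so nothing makes the timing of T1 comparable between arms.

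**Working it through.** The plan gives no figure to reproduce. The main check is a comparison of statements; the arithmetic only illustrates scale.

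**1. The statements side by side**

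| Section | Statement |
|---|---|
| Programme implementation | Baseline complete, then allocation |
| Blinding | Baseline is before randomisation and is T0 |
| Statistical methods | T0 and T1 are separate; T1 is tied only to the start of the intervention |
| Secondary outcome measures | Six instruments at T1 and T2, none at T0 |
| Data analysis plan | ANCOVA on baseline values, time point not named |

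If baseline means T0, the six instruments have no baseline. If T1 is their baseline, the T0 label in Blinding is wrong for them, and whether T1 precedes allocation is left open. On either reading the text needs reconciling.

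**2. Form of the bias if T1 follows allocation**

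Let B be the report a parent would have given before allocation, G the arm (0 or 1), d the shift in the T1 report caused by knowing the arm, and Y the T2 score with no true effect.

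- T1 report: X = B + d·G
- T2 score: Y = β·B + error = β·X − β·d·G + error

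The ANCOVA coefficient for arm is therefore −β·d, opposite in direction to the shift. This assumes that the shift does not persist to T2.

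**3. Illustrative size** (β and d are assumptions; the article gives neither)

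- β = 0.5, d = 0.2: 0.5 × 0.2 = 0.10 SD
- β = 0.6, d = 0.3: 0.6 × 0.3 = 0.18 SD
- β = 0.7, d = 0.5: 0.7 × 0.5 = 0.35 SD

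**4. Simulation check**

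There were 5,000 runs per setting, no true effect, and a two-sided 5% test from ANCOVA on the shifted T1 value. The article gives 16 per arm; 12 per arm is 16 × 0.75, after the full withdrawal allowance. Cells show mean bias in SD and rejection rate.

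| Per arm | Correlation | d = 0.2 | d = 0.5 |
|---|---|---|---|
| 12 | 0.3 | −0.061, 5.1% | −0.148, 7.3% |
| 12 | 0.5 | −0.103, 5.7% | −0.253, 9.4% |
| 12 | 0.7 | −0.134, 7.5% | −0.348, 19.4% |
| 16 | 0.3 | −0.063, 6.3% | −0.150, 6.5% |
| 16 | 0.5 | −0.093, 6.0% | −0.249, 11.7% |
| 16 | 0.7 | −0.135, 7.7% | −0.349, 25.0% |

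With d = 0, rejection was 4.6% to 5.4%. The simulated bias agrees with −β·d.

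**5. Yardstick**

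The approximate ANCOVA 95% half-width at 12 per arm is t(0.975, 21) × √(2/12) × √(1 − r²).

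- r = 0.5: 2.080 × 0.408 × 0.866 = 0.74 SD
- r = 0.7: 2.080 × 0.408 × 0.714 = 0.61 SD

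The unadjusted half-width, t(0.975, 22) × √(2/12) = 0.85 SD, is the wrong comparator because the bias arises in the adjusted model.

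**The case against.** The strongest reply is that this is a matter of labels and that the order is sound. No section places T1 after randomisation, and a visit before allocation is also before the intervention. Programme implementation describes eligibility confirmation and baseline assessment as steps at the recruiting centre, with allocation afterwards, and the MRI text links T0 to recruitment. T0 could be the recruitment step and T1 the rest of the baseline battery, both before allocation. The study flow figure, which is not available here, may show this. The two sections that speak directly about order both protect the baseline.

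Much of this stands. A reader might infer that T1 lies between allocation and the first home visit, and that the ANCOVA therefore adjusts for a post-randomisation variable. The article supports neither as fact: the position of T1 is open, and so is the ANCOVA baseline. The benign reading is still incomplete, because Blinding labels baseline T0 and the six instruments have no T0 value.

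A reader might also treat all six instruments as parent-reported. PDMS-2 is not described that way and outcome assessors are masked. An independent rater scores the observed EAS, although filmed behaviour could still reflect knowledge of the arm. For these two the problem is mainly timing.

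Finally, this is a pilot aimed chiefly at feasibility and acceptability, and even the largest illustrative bias lies within the interval half-width. That lowers the severity. It does not remove the conflict, because the results are meant to inform a larger trial and a larger sample does not remove a bias of this kind.

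**Conclusion.** The point holds as an internal contradiction. Two sections put baseline before randomisation, while the time-point definitions and instrument schedule give six secondary measures a single pre-treatment value at T1, which is not tied to randomisation and has no meaning for standard-care infants. Following the schedule as written permits, but does not require, collection after allocation.

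Any resulting bias is of unknown size. The range of 0.10 to 0.35 SD depends entirely on the assumed slopes and shifts and on a shift confined to T1. It applies only if T1 follows allocation and T1 is the covariate. Exposure is limited to the secondary outcomes. Severity: should-fix.

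**What to change.** **Text.** Reconcile Statistical methods and Secondary outcome measures with Programme implementation and Blinding. Complete the six measures, including COPM goal setting, in both arms before the REDCap allocation is released. They can be taken at T0, or at a T1 that is stated to precede allocation. Name that value as the ANCOVA baseline in the Data analysis plan.

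**Infants already enrolled.** Recruitment began in July 2018, so compare the T1 and randomisation dates for each infant. Where T1 values were taken after allocation, do not use them as the main covariate. Adjust for variables measured at T0 instead, and show the T1-adjusted result as a sensitivity analysis.

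**Cost.** Wording, the order of forms in REDCap and a date check. The EAS uses a 15-minute home video, so recording it before allocation needs some scheduling. No new measures are required.

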#### Feasibility and acceptability evaluation

Feasibility of recruitment process will include number of infants referred and eligible and proportion subsequently recruited. Parent engagement will be measured on the Pediatric Rehabilitation Measure of Engagement-General (PRIME-G).^33^

Adherence to the intervention will be assessed by documenting the number of withdrawals, retention rate and number completing the minimum number of intervention visits.

Acceptability will be measured by considering reasons for not consenting to participate in the RCT, intervention adherence through parent diaries and a post-intervention questionnaire to assess satisfaction and parent perceptions of the intervention using the Canadian Occupational Performance Measure (COPM). Parent enactment of delivery of the intervention with their child in the home will be assessed from parent-recorded videos and assessed using a fidelity checklist.^34^

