### Treatment receipt and enactment

#### Delivery and fidelity

The fidelity of the VISIBLE approach was illustrated using case studies. Throughout the study duration, VISIBLE therapists will receive continued training and peer support for the provision of programme from investigators with a speciality in vision intervention to ensure the intervention is carried out with fidelity.

As previously described,^32^ study therapists will video-record all home visit sessions, with recordings uploaded to a central server at the Queensland site. For each therapist delivering each intervention, the first two home visits will be independently reviewed by two study investigators at the Queensland site using the Provider Delivery Observational Checklist. Thereafter, a random selection of recordings will be reviewed throughout the study, such that approximately 10% of each therapist’s intervention sessions are evaluated using the same checklist. An 80% compliance threshold for checklist items will be applied; deviations beyond this threshold will prompt feedback to the study therapist’s local site supervisor. The supervisor and study therapist will then jointly review the feedback and identify strategies to reduce further deviations from the study protocol.

To monitor and enhance treatment receipt, study therapists will employ a range of strategies. Worksheets designed to support parents’ delivery of the intervention will be provided, including guidance on preparing for play sessions, prompts regarding optimal timing and environmental setup for play, and tools to encourage parent reflection on their play sessions with their child. During structured home visits, therapists will ask parents to demonstrate the intervention activities they have been practising with their child, as well as the materials used for goal-directed activities. Therapists will provide feedback and highlight the child’s progress.

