As the child advances toward established goals, therapists will demonstrate subsequent stages or goals of therapy and discuss features of toys, objects or environmental setups that may elicit the targeted behaviours. Coaching strategies will be used to support families in identifying toys and objects available within their own environment that could be incorporated into therapy activities. Collaborative discussions will help therapists determine whether parents understand the upcoming therapy goals. Families may also video-record their child during sessions as a prompt to support intervention delivery between therapist visits.

Parents will be interviewed independently when their infant is at baseline, midway through the intervention period and at 12 months corrected age. These interviews will explore parents’ responses to the intervention requirements, the feasibility of intervention delivery within their family context and their perceptions of changes observed in their child. Interviews will be conducted following completion of the Pediatric Rehabilitation Intervention Measure of Engagement, which was developed to capture parents’ perspectives on their own engagement in their child’s therapy.

The interview will follow parent’s completion of the Pediatric Rehabilitation Intervention Measure of Engagement, developed to gain parent’s perspective on their own engagement in their children’s therapy.^33^

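### The satisfaction part of acceptability is assigned to the COPM, which the protocol itself defines as perceived infant progress and also lists as a secondary outcome

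*Protocol article*

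**What the plan says.** The Abstract makes feasibility and acceptability the main objective, and the Aims list them separately from preliminary efficacy. Hypothesis H3 counts satisfaction among the components of acceptability, beside withdrawal rates and reasons and engagement scores, but names no tool for it.

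The tool is named under Feasibility and acceptability evaluation. That section begins "Acceptability will be measured by considering reasons for not consenting to participate in the RCT, intervention adherence through parent diaries" and adds, as the third source, "a post-intervention questionnaire to assess satisfaction and parent perceptions of the intervention using the Canadian Occupational Performance Measure (COPM".

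The Canadian Occupational Performance Measure (COPM) is then described under Secondary outcome measures, at T1 and T2, as a means of setting and ranking goals and of "measuring parent-perceived change of their infant’s performance of the goal and own satisfaction with progress". On the content of those goals: "The semi-structured initial interview to establish the goals will focus on what aspects of the infant’s vision behaviour the parent wants or needs" to see changed.

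Separately, the Delivery and fidelity section plans parent interviews at baseline, midway and 12 months corrected age. They cover how parents respond to what the programme demands, whether it can be delivered in their family, and what changes they see in the child. They follow completion of the parent engagement measure.

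**The concern.** The two sections give the COPM two different objects. In one, the parent rates the intervention. In the other, the parent rates the infant's goal performance and is satisfied, or not, with how far the infant has come. The document describes no COPM item or score about the programme itself: its burden, its usefulness, or its fit with family life.

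If the acceptability section is followed literally, the satisfaction result can mislead in either direction. A demanding programme would look satisfactory when the infant progresses, and a welcome one would look unsatisfactory when a severely affected infant does not. Any treatment effect on the COPM could also be reported twice, once as preliminary efficacy and once as acceptability, although the Aims keep these apart. A pilot meant to inform a larger trial needs to know whether parents will accept the programme independently of whether infants improve.

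**Working it through.** No arithmetic reproduces or refutes this point, because it turns on what an instrument measures. The check sets the sections side by side.

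**Step 1: what each section asks of the COPM.**

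| Section | Role of the COPM | Object of the parent's rating |
|---|---|---|
| Feasibility and acceptability evaluation | Acceptability, after the intervention | The intervention |
| Secondary outcome measures | Outcome at T1 and T2 | The infant's goal performance, and "performance of the goal and own satisfaction with progress" |

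The objects differ. The second row is the protocol's own definition, so no outside source on the instrument is needed.

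**Step 2: does the mismatch matter?** Consider the two cases in which the parent's view and the infant's course diverge.

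| Parent's view of the programme | Infant progress seen | COPM satisfaction as defined | Correct reading of acceptability |
|---|---|---|---|
| Burdensome | Yes | High | Low |
| Welcome | No | Low | High |

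In both, the COPM gives the wrong answer to the acceptability question. Where view and progress agree, it gives the right answer, but only because they agree.

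**Step 3: can progress occur without the programme?** The Abstract gives entry at 3–6 months and outcome at 12 months corrected age. The interval is therefore 12 − 6 = 6 months to 12 − 3 = 9 months. Over 6 to 9 months in the first year of life, some progress on goals can come from maturation alone. If the COPM is collected in both arms, as its listing among the outcomes implies, control parents will also have a satisfaction score. That score cannot be about VISIBLE.

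**Step 4: how much of acceptability rests on it?** The evaluation section names three sources.

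- Non-consent reasons come from families who did not enrol.
- Diaries record adherence.
- The COPM-based questionnaire is the only one of the three that asks enrolled parents what they think.

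Outside that list, H3 adds withdrawals and engagement scores, and the planned interviews ask about the programme's demands and its feasibility at home. None of these is defined by infant improvement, although the interviews also contain a part on perceived change in the child. The defect is thus confined to the satisfaction component.

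**The case against.** The strongest reply is that the wording is loose rather than wrong. The evaluation section speaks of a questionnaire, and a programme questionnaire may exist alongside the COPM. Using one instrument in two places is also not an error in itself: the COPM has a performance element and a satisfaction element, and the article does not say which serves which purpose. Both remarks are fair, but they do not remove the point. As printed, the COPM is the only instrument named for satisfaction, and its satisfaction element is defined as satisfaction with progress. If a separate questionnaire exists, the sentence still needs correcting.

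A reader might go further and infer that acceptability as a whole is scored by the COPM, so that acceptable would simply mean that the child improved. The document does not support this. No composite score and no COPM cut-off is defined, and burden could still show in the diaries, withdrawal reasons, engagement scores and interviews.

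A reader might also infer a parallel fault in the measurement of enactment. The evaluation section says "Parent enactment of delivery of the intervention with their child in the home will be assessed from parent-recorded videos", while Delivery and fidelity says "Families may also video-record their child during sessions as a prompt to support intervention delivery between therapist visits", which could suggest that only families who choose to film are measured. That does not follow. The optional filming is a memory aid for parents; the enactment videos are a separate item, stated without condition. Nor would it clearly help to substitute the visit recordings ("study therapists will video-record all home visit sessions"). The protocol treats parents' demonstrations at visits as a check on treatment receipt, and they do not show what parents do between visits. No change to enactment is asked for here.

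**Conclusion.** The point holds for the satisfaction component of acceptability. The two sections contradict each other on what the COPM measures and must be reconciled. As written, that component would reflect perceived infant progress and would overlap with a secondary outcome. The other acceptability sources stand.

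The bias cannot be sized from the document, and its direction depends on the infants' course: upwards where infants progress, downwards where they do not. The conclusion rests on taking the protocol's own description of the COPM at face value. It does not depend on the COPM being collected in both arms, although that would make the overlap plainer. The trial's validity is not in question, but the matter should be settled before acceptability is analysed, because views of the programme cannot be recovered from COPM scores.

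**What to change.** - Under Feasibility and acceptability evaluation, remove the COPM as the measure of satisfaction and perceptions. Keep it under Secondary outcome measures only.
- In its place, name the parent interviews already planned under Delivery and fidelity, in the VISIBLE arm. Use the parts on response to the programme's requirements and on feasibility within the family, and report the part on perceived change in the child separately.
- Put a few direct items on satisfaction with the programme in the post-intervention questionnaire, so that the component also has a result that can be tabulated. If such items already exist, say so and correct the sentence.

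The cost is a change of wording and, at most, a few added questions for parents. No further infant assessment is needed. The article gives a start in July 2018, so some families may already have passed the 12-month assessment. For them the interviews, if held as planned, are the available source, and the report should state how many families answered the direct items.
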